## Abstract

**Background:**

Until recently, strength training in children with cerebral palsy (CP) was considered to be inappropriate, because it could lead to increased spasticity or abnormal movement patterns. However, the results of recent studies suggest that progressive strength training can lead to increased strength and improved function, but low methodological quality and incomplete reporting on the training protocols hampers adequate interpretation of the results. This paper describes the design and training protocol of a randomized controlled trial to assess the effects of a school-based progressive functional strength training program for children with CP.

**Methods/Results:**

Fifty-one children with Gross Motor Function Classification Systems levels I to III, aged of 6 to 13 years, were recruited. Using stratified randomization, each child was assigned to an intervention group (strength training) or a control group (usual care). The strength training was given in groups of 4–5 children, 3 times a week, for a period of 12 weeks. Each training session focussed on four exercises out of a 5-exercise circuit. The training load was gradually increased based on the child's maximum level of strength, as determined by the 8 Repetition Maximum (8 RM). To evaluate the effectiveness of the training, all children were evaluated before, during, directly after, and 6 weeks after the intervention period. Primary outcomes in this study were gross motor function (measured with the Gross Motor Function Measure and functional muscle strength tests) and walking ability (measured with the 10-meter, the 1-minute and the timed stair test). Secondary outcomes were lower limb muscle strength (measured with a 6 RM test, isometric strength tests, and a sprint capacity test), mobility (measured with a mobility questionnaire), and sport activities (measured with the Children's Assessment of Participation and Enjoyment). Spasticity and range of motion were assessed to evaluate any adverse events.

**Conclusion:**

Randomized clinical trials are considered to present the highest level of evidence. Nevertheless, it is of utmost importance to report on the design, the applied evaluation methods, and all elements of the intervention, to ensure adequate interpretation of the results and to facilitate implementation of the intervention in clinical practice if the results are positive.

**Trial Registration:**

Trial Register NTR1403

## Background

Cerebral palsy (CP) is the most common cause of movement disability in childhood, with an incidence of 1.5–2.5 per 1000 live born children[1]. It is a non-progressive disorder that covers a number of neurological conditions, resulting in an abnormal development of movement and postural control[2]. From the perspective of the International Classification of Functioning, Disability and Health (ICF)[3], CP patients present with impairments in body function such as spasticity, low muscle strength, and selective motor control. These impairments may limit the performance of activities and participation in daily life. Improving and optimizing activities and participation are important treatment goals for therapeutic interventions.

A recent review has shown that low muscle strength, and not spasticity, causes the greatest limitations in motor function in children with CP[4], and this has shifted the focus from spasticity management towards strength training for these children. To be successful, strength training must be individualized, and should involve a progressive increase in intensity, thereby stimulating strength gains that are greater than those associated with normal growth and development (i.e. "overload")[5]. This is known as Progressive Resistance Exercise (PRE)[6], and for this type of exercise any method can be used to bear, overcome or resist force, such as body weight, free weights or machines.

Until recently, PRE was thought to be inappropriate, or potentially dangerous for children with CP because of the unfounded assumptions that such training would increase spasticity[7]. However, this concern is not supported by the results of recent studies which have shown that PRE strength training programs can improve lower limb muscle strength in patients with CP without increasing spasticity [8-11]. These results have been summarised in recent reviews [12-14], in which it was further concluded that PRE strength training *can *increase muscle strength, but that the effects are probably over-estimated because of the low methodological quality of these studies[12], and that future studies should furthermore develop more functional training programs aiming at a maximal carry-over into everyday activities[13].

Recently, new randomized clinical trials (RCT's) have been carried out to evaluate the effect of this type of functional strength training[10,15,16] in children with CP. Conflicting results were found on isometric muscle strength[15,16], gross motor function[10,15,16] and walking ability[10,16]. This might be due to the slightly different evaluation methods, but more probably to the differences in relevant training characteristics, such as type of training (e.g. home or school based), intensity (e.g. load based on body mass or repetition maximum), progression (e.g. none, weekly, individually based) and duration of the training (e.g. 5 or 12 weeks). Unfortunately, this information was not always provided, which hampers correct interpretations. For an adequate interpretation of the effectiveness of the intervention, standardisation and reporting on all relevant aspects of the training is therefore of utmost importance.

For PRE strength training, the key principle should always be standardized: the timely progression in strength intensity based on the child's *individual *level of strength, to ensure the principle of progressive overload[17,18]. This is best assessed by the repetition maximum (RM), which is the maximum number of repetitions that can be performed correctly under a given load. The heaviest load with which an exercise can be performed for 1 complete repetition with correct performance is the 1 RM. According to current guidelines, training should start with a dynamic warm-up period, initially 1 or 2 sets of 8–15 repetitions with a light to moderate load (about 30–60% 1 RM) to learn the right technique, and then progress to 3–5 sets of 8–15 repetitions[19]. Loads can safely be progressed to 70–85% of 1 RM[20]. A training frequency of at least 2 non-consecutive days per week is further recommended. In addition, for children the training should be fun, and group-training is thought to increase both the fun and the individual motivation to progress.

It is therefore thought that individualized, but group-given, school-based, functional PRE strength training, with sufficient frequency, intensity and progression, increases the effectiveness of the training, although these aspects need further investigation. The purpose of this study was to evaluate, in an RCT, the effectiveness of such functional PRE lower limb strengthening program in a group of children with CP. A protocol was therefore developed to train lower limb muscle strength, based on the current guidelines for PRE strength training in healthy adults[6] and children[17,19], the recent literature on strength training for CP [12-14], and the expertise of experienced paediatric physical therapists in the Netherlands. In this protocol, the frequency, duration, weekly intensity and progression on the basis of RM testing of the training, and also the type and technique of each of the exercises were standardized. We hypothesize that children who will follow this structured functional PRE strength training program will increase in muscle strength, which accordingly will lead to functional improvement in gross motor function and walking ability, but with no negative effect increasing spasticity or decreasing range of motion, compared to children receiving usual care. This paper describes the study design and all relevant elements of the functional PRE strength training protocol.

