### Sample size

At least 42 children were required to detect a difference in improvement of 5% on the Gross Motor Function Measure (GMFM) between the intervention group and the control group, with a power of 0.8 and an alpha of 0.05. To allow for some drop-outs, we aimed to recruit at least 50 children (25 intervention, 25 control).

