### Adverse outcomes

*The Range f Motion *in the hamstrings, adductors, rectus femoris, soleus and gastrocnemius muscles was assessed with goniometry during the third of three slow passive stretches (>3 seconds)[34].

#### 

*Spasticity*. Goniometry was also used to measure spasticity in the hamstrings, adductors, rectus femoris, soleus and gastrocnemius muscles by assessing the joint angle at which a 'catch' (defined as a sudden increase in muscle tone, blocking further movement) occurred in a fast passive stretch (<1 second)[35].

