### Data-analyses

Student T-tests (continuous data, if normally distributed), Mann-Whitney tests (continuous data, if not normally distributed), and Chi-square tests (dichotomous and ordinal data) will be used to evaluate group differences at baseline. Differences in change from baseline between the intervention group and control group for the three post baseline assessments will be evaluated by means of generalized estimating equations (GEE) for longitudinal analysis[36]. GEE is appropriate for analyzing longitudinal data with hierarchically structured data and the advantage of GEE is that this method takes into account the dependency of repeated measures within the same person. To determine the effect of the strength training program, changes in the training group will be compared to the changes in the control group (interaction between group * time).

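### The no-harm half of the hypothesis (spasticity, range of motion) is paired only with a between-group difference analysis, which cannot establish it at this sample size

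*Protocol article*

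**What the plan says.** The hypothesis at the end of the Background has two parts. The first is a gain in strength, carried over into gross motor function and walking. The second concerns harm: "but with no negative effect increasing spasticity or decreasing range of motion, compared to children receiving usual care". It is worded as a comparison with the control arm.

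The abstract gives the role of these measures: "Spasticity and range of motion were assessed to evaluate any adverse events". The Adverse outcomes section lists five muscles for range of motion and the same five for spasticity ("Goniometry was also used to measure spasticity in the hamstrings, adductors, rectus femoris, soleus and gastrocnemius muscles"), so ten joint angles in all.

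Data-analyses describes one between-group method for follow-up data. "Differences in change from baseline between the intervention group and control group for the three post baseline assessments" are evaluated by GEE, and for the training effect "changes in the training group will be compared to the changes in the control group (interaction between group * time"). The section mentions no acceptable worsening, no non-inferiority or equivalence comparison, and no use of a confidence bound. It also does not say how a null result on an adverse outcome is to be read.

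The Sample size section rests on one outcome: "At least 42 children were required to detect a difference in improvement of 5% on the Gross Motor Function Measure (GMFM"), with power 0.8 and alpha 0.05. The recruitment target was 25 per arm, and the abstract reports 51 children recruited.

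**The concern.** A comparison built to detect a difference can contradict a claim of no harm, but failing to detect one does not confirm the claim. When the hypothesis is that the intervention does no harm and the only stated comparison is a difference, the sole outcome of that comparison that agrees with the hypothesis is non-significance. Such agreement comes more easily the smaller or noisier the study is.

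The question matters in this field. The Background explains that progressive resistance training was long avoided in these children because it was feared to increase spasticity. It calls that fear unfounded, but also reports that reviewers judged the earlier trials to be of low methodological quality. A randomised trial that reports no negative effect would carry weight, so the statement should rest on what the data exclude rather than on what they fail to show.

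**Working it through.** **Inputs.** From the article: 42 children as the minimum (21 per arm), 25 per arm as the target, 51 recruited, power 0.8, alpha 0.05, five muscles for each of two properties. Not given: the SD of change for the GMFM or for any angle, and any margin. The harm calculations are therefore in SD units of the change score. They assume independent children, two equal arms, a two-sided 5% level, and one measure at one post-baseline time point.

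**1. The plan's own figure.** n per arm = 2(z₀.₉₇₅ + z₀.₈)²(SD/5)². Solving backwards for n = 21:

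SD = 5 / [(1.960 + 0.842) × √(2/21)] = 5 / 0.865 = 5.78 GMFM points (5.64 with the t distribution).

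The figure of 42 is plausible but cannot be confirmed without an SD. It implies a standardised difference of about 0.86 to 0.89. The trial was thus sized for a large effect on a different outcome.

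**2. Width of the interval for a harm measure.** Half-width = t₀.₉₇₅,₂ₙ₋₂ × √(2/n), in SD units.

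| n per arm | t | √(2/n) | half-width |
|---|---|---|---|
| 21 | 2.021 | 0.309 | 0.62 SD |
| 25 | 2.011 | 0.283 | 0.57 SD |

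**3. Chance that a real worsening is non-significant.** Noncentral t with noncentrality δ/√(2/n). For δ = 0.5 SD:

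- n = 25: noncentrality 0.5/0.283 = 1.77, power 0.410, non-significant 59%.
- n = 21: noncentrality 0.5/0.309 = 1.62, power 0.353, non-significant 65%.

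For δ = 0.8 SD the corresponding figures are 21% and 28%. With 51 recruited, the 21-per-arm row applies only after nine losses.

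**4. What the interval could exclude if there were truly no harm.** By symmetry, the chance that the 95% interval excludes a 0.5 SD worsening when the true difference is zero equals the power above: 41% (n = 25) or 35% (n = 21). With 25 per arm, an 80% chance is reached only for a margin of about (1.960 + 0.842) × 0.283 = 0.79 SD (normal approximation). A margin of 0.5 SD at one-sided 0.025 and 80% power would need 126 children in total. These margins are illustrations, not proposals.

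**5. Several muscles at once.** Step 3 is for a single measure. If every measure worsened by 0.5 SD (25 per arm, assumed correlation between measures 0.3 to 0.7), simulation puts the chance that none shows a significant worsening at about 17 to 32% for five measures and 7 to 24% for ten. A worsening confined to one muscle keeps the 59%.

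**6. What could move these figures.** Using the three post-baseline assessments or adjusting for baseline could narrow the interval. Correlation among children trained in the same group could widen it. Neither makes a non-significant difference into evidence of no harm.

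**The case against.** The strongest reply is that the article nowhere says a null result will count as proof of safety. Data-analyses only says that changes will be compared, names no significance rule for follow-up data, and describes a model from which a confidence interval follows directly. That stands. A reader might infer that non-significance will be presented as proof of no harm, or that the safety conclusion is invalid whatever the data show. The article supports neither. It gives no rule for reading a null result, a significant worsening would contradict the hypothesis, and an interval that excluded any worsening of concern would support it.

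A second reply is that these are adverse outcomes in a trial of effectiveness, and that looking for group differences in safety measures within a trial sized for efficacy is ordinary practice. This also stands, and it limits the remedy: a powered non-inferiority comparison for each muscle is not required. It does not remove the mismatch, because the article itself puts the no-harm statement inside the hypothesis as a comparison with usual care.

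A third reply is that an article condenses a fuller plan, and that a margin or interval criterion may be given there. The absence of a margin alone would not be a finding. The point is that two elements the article does state, the hypothesis and the method offered to evaluate it, do not fit together.

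Finally, the 59% applies to one muscle at one time point. A general worsening would be noticed more often, as step 5 shows. That limits the size of the problem but does not refute it.

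**Conclusion.** The point holds in a limited form. The stated analysis cannot establish the no-harm part of the hypothesis; as written, only a non-significant difference could be offered in its support. With about 25 per arm, a single harm measure at a single time point is estimated to within about ±0.57 SD of change, and a true 0.5 SD worsening on it would be non-significant about 59% of the time.

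These figures assume independent children and a simple two-arm comparison. They cannot be turned into degrees without an SD that the article does not give. The weakness lies in how the claim is framed and judged. It does not touch the primary outcomes or the choice of GEE. It should be put right, but it does not threaten the trial.

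**What to change.** In Data-analyses, add that range of motion and spasticity are judged by the 95% confidence interval of the between-group difference in change from the GEE already planned. The limit in the direction of worsening should be reported for each muscle, in the form of a mean worsening of more than X degrees being excluded. Add that a non-significant difference is not taken as evidence of no harm.

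Then choose one of two courses for the hypothesis. If the sponsor wishes to claim no negative effect, its clinicians should fix the largest acceptable worsening before the data are analysed, and the claim should depend on the worse-direction limit lying inside it. Otherwise, that part of the hypothesis should be reworded as descriptive safety monitoring.

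The cost is a few sentences, with no new data and no change of model. The downside is that the safety conclusion may have to be reported as inconclusive.

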## Methods

### Design

The study has a single-blinded, randomized controlled design and the study protocol was approved by the Medical Ethics Committee of the VU University Medical Center in Amsterdam, the Netherlands.

### Setting

The training and assessments took place in three special schools for physically disabled children in the Netherlands, from which all the children were recruited.

### Participants

All the participants were ambulatory children with spastic unilateral or bilateral CP[2,21]. The inclusion criteria were: 1) age between 6 and 13 years; 2) able to accept and follow verbal instructions; 3) ability to walk independently indoors, with or without walking aids (Gross Motor Function Classification System [GMFCS][22] levels I – III); 4) able to participate in a group training program. Children were excluded if they had instable seizures, if they had received treatment for spasticity or surgical procedures up to 3 months (for botulinum toxin type A injections) to 6 months (for surgery) prior to the study (or planned in the study period); if any change in medication was expected during the study period; or if they suffered from other diseases that interfered with physical activity.

A paediatric physiatrist working in each school pre-selected the children, based on the inclusion and exclusion criteria. The parents of the children who met these criteria received written information about the study. Accordingly, the parents of each potential participant were contacted by a researcher who gave further oral explanation, and answered any questions, if necessary. Written informed consent was given by the parents, and all children who were over 12 years of age. After all the informed consents had been collected, randomization was performed per school. The children were randomly allocated according to three stratification variables: GMFCS level (I; II–III); age (youngest: 6–9 years; oldest 10–13 years), and gender (boy; girl). Families were notified by means of a letter of their child's allocation to the intervention group or the control group prior to the first baseline assessment.

### Sample size

At least 42 children were required to detect a difference in improvement of 5% on the Gross Motor Function Measure (GMFM) between the intervention group and the control group, with a power of 0.8 and an alpha of 0.05. To allow for some drop-outs, we aimed to recruit at least 50 children (25 intervention, 25 control).

### Intervention: Lower Limb Strength Training

The intervention group followed a 12-week functional PRE strength training program (not including holidays), 3 times a week. Each training session lasted for 45–60 minutes.

The training replaced the conventional physical therapy program, when this was consistent with the objectives of the strength training (improvement of functional abilities by increasing muscle strength/fitness), but was additional to any other therapies (e.g. swimming, occupational therapy). The strength training was specifically designed to strengthen the anti-gravity muscles of the lower limbs (such as the glutei, vasti, gastrocnemius, soleus), while performing functional exercises in a circuit training.

#### Circuit training

The training sessions were held in small groups (± 4–5 children) with a 5-station circuit, supervised by two experienced physical therapists per group. During each training session, the children wore their regular (street) shoes, splints, trousers, and they all wore a group T-shirt to stimulate the group-feeling. Each training session started and finished with a warming up and cooling down period of 5–10 minutes, during which muscle stretching exercises and aerobics were performed. During the main training phase, each child performed 4 different exercises on the 5-station circuit. The different stations of the circuit were named as followed: leg-press, loaded sit-to-stand, loaded game, unloaded game and relax. Table 1 presents the characteristics of the 5-station circuit.

**Table 1 T1:** Characteristics and training volumes of the 5-station circuit

**Station**	**Load**	**Trained Leg**	**Exercise**	**Functional**	**Supervision**	**Game**	**Resistance**
1. Leg-press	High	Bilateral	Leg-press	No	Very strict	No	Leg-press
2. Loaded sit-to-stand	High	Bilateral	Sit-to-stand	Yes	Very strict	No	Weight vest
3. Loaded game	Low	Unilateral	Half-knee rise; Lateral step up; Forward step up; (Sit-to-stand)	Yes	Strict	Yes	Weight vest
4. Unloaded game	No	Unilateral	Half-knee rise; Lateral step up; Forward step up; (Sit-to-stand)	Yes	Strict	Yes	Body weight
5. Relax	n.a.	n.a.	n.a.	n.a.	none	n.a.	n.a.

Abbreviation: n.a. = not applicable

The exercise stations were a combination of high load (e.g. leg-press and loaded sit-to-stand stations), low load (e.g. loaded game station) and no load (e.g. unloaded game station) exercises (see Table 1; the exercises are explained in more detail in Additional files 1 to 4).

At the stations that were highly loaded (e.g. leg-press and loaded sit-to-stand stations), both legs were trained simultaneously by means of bilateral exercises. The exercises at these stations were fixed: a leg-press exercise (see Additional file 1) and a loaded sit-to-stand exercise (see Additional file 2). Of these, only the loaded sit-to-stand is a functional exercise, resembling an everyday activity with which ambulatory children with CP may experience difficulty (i.e. rising from a chair).

At the stations that were low or not loaded (e.g. loaded game station and unloaded game station), the most affected leg was (preferably and if possible) trained by means of unilateral exercises. All exercises at these stations were functional. These exercises were randomly chosen by the physical therapist: a lateral step up exercise or a forward step up exercise (i.e. climbing a stair or stepping up onto a kerb, see Additional file 3), or a half-knee rise exercise (i.e. rising from the ground, see Additional file 4). If a child was not able to perform these unilateral exercises, the sit-to-stand exercise (see Additional file 2) could be performed instead.

At the stations that were highly loaded (e.g. leg-press and loaded sit-to-stand stations), correct performance of the exercises was mandatory and required very strict supervision (close one-on-one guidance per child by the physical therapist). At the stations that were less or not loaded (e.g. loaded game station and unloaded game station), somewhat less supervision was needed for these exercises (one-on-two guidance per two children by the physical therapist, so that the children could perform the exercises together). Furthermore, it was also important that the children enjoyed the training. Therefore, the exercises at the loaded game and unloaded game stations could be chosen at random. In addition, the exercises at these stations were suitable to be integrated in a game-like situation (for example: playing skittles), which could be performed together or as a competition.

At the leg-press station resistance was applied by the leg-press machine itself, which was specifically adapted for children by means of an elevated footplate (EN-Dynamic Seated Leg Press, Enraf Nonius, The Netherlands). At the other loaded stations, where functional exercises were performed, resistance was applied by means of a customised weight vest (see Figure 1).

